### Hypotheses

3.2

The RTS intervention improves the therapeutic relationship between nurses and patients hospitalized in mental health units.Hypothesis 1Inpatients receiving the RTS intervention by their referent nurse will have a higher difference in mean score relative to inpatients receiving standard care on the therapeutic relationship measure using the Working Alliance Inventory‐Short scale (WAI‐S).
Hypothesis 2Patients receiving the RTS intervention by their referring nurses will obtain a higher mean score difference compared to patients receiving standard care when measuring psychiatric quality of care using the Quality in Psychiatric Care (QPC) scale.
Hypothesis 3Patients receiving the RTS intervention by their referring nurses will obtain a lower mean score difference compared to patients receiving standard care on the measurement of perceived coercion using the Coercion Experience Scale (CES) instrument.

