### Outcome measures

3.9

The Working Alliance Inventory Short Questionnaire (WAI‐S), patient version. This is an instrument for measuring the working alliance, and therefore, the therapeutic relationship between professional and patient (Horvath & Greenberg, 1989). The short version of the WAI has 12 items, each item is rated by the professional and the patient on a Likert scale ranging from 1 (never) to 7 (always). This instrument is made up of three factors: bonding, agreement on objectives and agreement on tasks. The Spanish adaptation of Andrade‐González and Fernández‐Liria (2015) presents Cronbach's *α* values of 0.93 for the total scale and 0.85, 0.81 and 0.90 for each of the factors.The Quality in Psychiatric Care scale (QPC: Schröder et al., 2007) assesses the quality of care and is the best suited to evaluate the quality of care in psychiatric units. The QPC contains 30 items and each item is evaluated by means of a Likert scale with four response options, where 1 indicates total disagreement and 4 indicates total agreement. It is composed of six dimensions: therapeutic relationship, patient participation, support received, environment, safety and hospital discharge. The maximum score is 120 points, and the minimum is 30 points. A high score in each dimension or in the total scale would indicate a very good perception of quality on behalf of the patient. The Spanish version will be used (Sanchez‐Balcells et al., 2021) which presents a Cronbach's *α* of 0.94 for the total scale and for five of the six dimensions it was over 0.7, except for the dimension measuring the environment, which was 0.67.The Coercion Experience Scale (CES‐18: Bergk et al., 2010). This scale assesses the subjective experience of coercion during psychiatric hospitalization. The CES‐18 in its short version consists of 18 items that are divided into 2 dimensions, one measuring coercion and humiliation and the other fear, on a five‐point Likert‐type scale (1‐never and 5‐always); where participants rate and record their own evaluation and self‐perception of the coercive intervention experienced. This instrument was validated in a Spanish population by Aguilera‐Serrano et al. (2019), which presents a Cronbach's *α* of 0.94 for the total scale and 0.93 and 0.71 for its two factors.

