### Recruitment and data collection

3.10

Once the centres have been randomized and the collaborating nurses of the units where the intervention will be carried out have been trained, the person from the research team coordinating the study in each unit will be responsible for informing the patients who meet the inclusion criteria between 24 and 72 h from the time of admission about the objectives of the study and will obtain informed consent. Patients will be recruited consecutively and will receive a confidential code assigned by the project coordinator, which will be their identification for the data collection dossiers. In the case of patients from centres chosen for the intervention, one of the nurses who has received the training will be assigned to the patient. In the case of control centres, the usual process of assigning a nurse from the unit will be followed and the nurse will not have any notification in this regard. In both cases, once the first meeting or welcome interview by the referring nurse in the unit has taken place, the baseline assessment (T1) will be carried out by a nurse who is not involved in the patient's care process and who has been previously trained in the measurement instruments. The baseline assessment will be included in the T1 dossier and will consist of administering the WAI‐S and QPQ instruments. Prior to discharge, the same person outside the care process of the hospitalized person will administer the instruments to the user for the follow‐up assessment included in the T2 dossier, which will include the WAI‐S, the QPC and the CES (T2). The remaining data will be obtained from the patient's clinical history and will be collected by the centre's principal investigator through the data collection dossier.

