### Data analysis

3.11

The research team will have a common space through a web platform to create and manage data. In this platform, a database will be generated for each centre to which only the researchers of each centre and the methodological team will have access. Also, a common database will be generated for all the centres to which only the project coordinator and the members of the methodological team will have access. The researchers of each centre will register the data in the specific database of each centre and will send the results in parallel to the study coordinator, who, through the methodological team, will also register the data in the common database. This will ensure the double entry of the data.

Descriptive statistics will be used to describe the sociodemographic and clinical characteristics of the patients through means and standard deviations (SD); frequencies and proportions. The chi‐square test (χ^2^) and the t‐test for independent samples will be used to detect any significant differences between the intervention and control groups on baseline variables. A repeated measures analysis of variance will be performed to analyse the relationship of the intervention with each of the dependent variables by introducing sociodemographic and clinical characteristics into the model.

To evaluate the effectiveness of the intervention, a multivariate analysis of covariance analysis (MANCOVA) will be performed, introducing the pretest‐posttest differences in the quality of the therapeutic relationship, the quality of psychiatric care and the perception of coercion as dependent variables. Statistical analyses will be performed using SPSS v27.

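### The effectiveness MANCOVA needs a pretest-posttest difference in coercion, but the CES is administered only at T2, so the analysis cannot be run as written

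*Protocol article*

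**What the plan says.** The assessment schedule is in section 3.10 (Recruitment and data collection). For T1: "The baseline assessment will be included in the T1 dossier and will consist of administering the WAI‐S and QPQ instruments". For T2, before discharge, it describes "the follow‐up assessment included in the T2 dossier, which will include the WAI‐S, the QPC and the CES (T2"). QPQ is not defined anywhere in the article and is evidently a slip for QPC. On other data the section says: "The remaining data will be obtained from the patient's clinical history".

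Section 3.11 (Data analysis) plans two models. One is a repeated measures analysis of variance for each of the dependent variables, with sociodemographic and clinical characteristics added. The other, introduced as the evaluation of effectiveness, is a MANCOVA, "introducing the pretest‐posttest differences in the quality of the therapeutic relationship, the quality of psychiatric care and the perception of coercion as dependent variables".

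Section 3.2 states Hypothesis 3 in similar terms: patients receiving the intervention "will obtain a lower mean score difference compared to patients receiving standard care on the measurement of perceived coercion", using the CES. Section 3.9 says of the CES: "This scale assesses the subjective experience of coercion during psychiatric hospitalization". Patients rate it themselves.

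**The concern.** A pretest-posttest difference needs a pretest. The schedule gives the CES one administration, at the end of the stay, while the analysis treats it as if it had two. The article states both the schedule and the model, and they cannot both be followed. This is not a detail left to an analysis plan, because no later document can supply a baseline that was never measured.

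The MANCOVA is the model that the article attaches to the evaluation of effectiveness. If it fails when first run, someone must choose a replacement with the data in hand: drop coercion, mix a T2 score with two change scores, or fit separate models. These choices can give different answers on one of the three numbered hypotheses, and in the multivariate test they can change the result for all three outcomes together.

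**Working it through.** **1. CES measurements available, against what the models need**

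| Instrument | T1 (section 3.10) | T2 (section 3.10) | Pre-post difference (section 3.11) |
|---|---|---|---|
| WAI-S | yes | yes | can be formed |
| QPC | yes (written QPQ) | yes | can be formed |
| CES | no | yes | cannot be formed |

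QPQ cannot stand for the CES, since the T2 list names the QPC and the CES separately. The only other data source is the clinical history, which cannot hold a self-rated CES.

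**2. Effect on the MANCOVA.** The model uses patients who have all dependent variables. Planned patients: 2 × 131 = 262 (section 3.6). Patients with a CES difference: 0. Complete cases for the three-difference model: 0 of 262, and likewise 0 among those who complete follow-up.

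**3. Effect on the repeated measures ANOVA.** It needs at least two measurements of each outcome. The WAI-S and the QPC have two; the CES has one. The ANOVA can be run for the first two only.

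**4. The design's own sample size rests on change scores.** Inputs from section 3.6: two-sided alpha 0.05, power 0.80, difference 3, SD 10, pre-post correlation 0.7, loss 20%.

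- SD of change = 10 × √(2 × (1 − 0.7)) = 7.746
- n per group = 2 × [7.746 × (1.960 + 0.842) / 3]² = 104.65
- With 20% loss: 104.65 / 0.8 = 130.8, that is 131, the stated figure (132 if 104.65 is first rounded up to 105)

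Other formulas do not give 131. An ANCOVA variance gives 89 per group, or 112 after loss. A T2-only comparison gives 175, or 219 after loss. So the calculation assumes a pre-post difference, which the CES does not have.

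**5. What a T2-only CES comparison could detect (illustration).** The article gives no SD or target difference for the CES. Purely as an assumption, take SD 10 and difference 3 from section 3.6:

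| Per group | Power, change score (r = 0.7) | Power, T2 only | Detectable difference at 80% power, T2 only |
|---|---|---|---|
| 105 | 80% | 58% | 3.87 |
| 131 | 88% | 68% | 3.46 |

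These figures ignore clustering by unit. They show the direction of the loss, not its size for the CES.

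**The case against.** The strongest reply is about grammar. The list in section 3.11 could be read as the pre-post differences in relationship and care quality, plus perception of coercion as a T2 score. A MANCOVA on two change scores and one T2 score can be computed, and that reading fits the schedule. But it is strained, since one phrase governs all three constructs. It also leaves the repeated measures ANOVA, planned for each of the dependent variables, impossible for the CES.

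Three points on scope stand:

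- The main objective and Hypothesis 1 concern the therapeutic relationship. The WAI-S is measured at both times, so its change can be analysed, and so can the QPC's.
- Hypothesis 3 is ambiguous. Its wording can mean a between-group difference in mean CES, which T2 data can test, though not by the analysis stated.
- The count of 0 of 262 applies only to the MANCOVA on three differences. It does not mean that the trial has no analysable patients.

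None of this reconciles the schedule with the model.

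**Conclusion.** The concern holds. As written, the MANCOVA named for effectiveness has no analysable patient (0 of 262), and no pre-post analysis of coercion is possible. The damage is confined to the three-variable model and to every change analysis of the CES; the separate WAI-S and QPC change analyses survive, as does a T2 comparison of the CES. The conclusion rests on two readings, both well supported: that QPQ means QPC, and that the differences in section 3.11 cover all three constructs. It depends on no assumed number. It must be fixed, because the stated effectiveness analysis would otherwise be replaced after the data are seen.

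**What to change.** In section 3.11, remove coercion from the pretest-posttest MANCOVA and from the repeated measures ANOVA, leaving the WAI-S and the QPC. State a separate analysis for coercion: a between-group comparison of the CES-18 total at T2. A mixed model with a random intercept for unit would suit allocation by unit. It could adjust for admission characteristics in the clinical history that precede the intervention, such as involuntary admission. The random intercept and the covariates are advisable but are not needed to cure the contradiction. Reword Hypothesis 3 to a lower mean CES score at T2, and correct QPQ to QPC in section 3.10.

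The cost is a few sentences and no new data collection. A T2-only analysis may have less power than a change score, so the article should not imply that the 131 per group was sized for the CES.

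The alternative is to add the CES to the T1 dossier. That would also reconcile the sections, but it changes data collection. The meaning of a baseline so soon after admission would also need justification, because the scale rates coercion during the hospitalization itself. The T2 comparison fits the instrument better. Whichever is chosen, it should be fixed before the outcome data are examined.

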### Sample size

3.6

Accepting an alpha risk of 0.05 and a beta risk of 0.2 in a bilateral contrast, 131 subjects in the first group and 131 in the second group are required to detect a difference equal to or greater than 3 units. The common standard deviation is assumed to be 10 with a correlation coefficient between the initial and final measurement of 0.7. A loss‐to‐follow‐up rate of 20% was estimated.

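### The effectiveness analysis uses pretest-posttest differences without naming the T1 score as a covariate, which is valid but gives up about 15% in variance under the plan's own assumptions

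*Protocol article*

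**What the plan says.** Section 3.11 (Data analysis) describes two models.

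- A repeated-measures analysis of variance for each dependent variable, with sociodemographic and clinical characteristics in the model.
- A MANCOVA to evaluate effectiveness, "introducing the pretest‐posttest differences in the quality of the therapeutic relationship", in the quality of care and in perceived coercion as the dependent variables. No covariates are listed for this model, and the T1 score is not named in either.

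The design values in section 3.6 (Sample size) are a two-sided alpha of 0.05, power of 80%, a target difference of 3 units and a common SD of 10. The calculation also relies on "a correlation coefficient between the initial and final measurement of 0.7". Allowing for 20% attrition, the plan arrives at 131 per group.

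Section 3.10 (Recruitment and data collection) has WAI-S and QPC (printed there once as QPQ) collected at T1 and again at T2 before discharge. CES is collected at T2 only.

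**The concern.** When a baseline score is available and correlates with the final score at less than 1, regressing the final score on the baseline gives a smaller residual variance than subtracting the baseline. Subtraction fixes the slope at 1. With equal SDs at both visits, the plan's correlation implies a slope of 0.7.

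Neither planned model escapes this. With two visits, the group-by-time test of a repeated-measures ANOVA is a comparison of mean change between groups, so it is the same change-score analysis as the MANCOVA applies to each scale.

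Precision is at stake, and this trial has reason to want it. Twelve units are randomized (sections 3.4 and 3.7), but the calculation in section 3.6 makes no allowance for clustering, so true power is likely to be below the nominal 80%. The T1 scores needed for adjustment are already collected for WAI-S and QPC.

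**Working it through.** **Inputs (section 3.6):** two-sided alpha 0.05 (z = 1.960), power 0.80 (z = 0.842), difference 3, SD 10, correlation ρ = 0.7, loss 20%.

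**Step 1. Reproduce the plan's figure.**

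- Variance of the change score: 2 × SD² × (1 − ρ) = 2 × 100 × 0.3 = 60 (SD 7.746).
- n per group = 2 × 60 × (1.960 + 0.842)² / 3² = 104.65, so 105 completers.
- With 20% loss: 104.65 / 0.8 = 130.8, so 131.

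Other outcome definitions do not give 131. T2 alone (variance 100) needs 175 completers, or 219 with loss. T2 adjusted for T1 needs 89, or 112 with loss. The trial is therefore sized on the unadjusted change score.

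**Step 2. Variance after adjustment for T1.**

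- SD² × (1 − ρ²) = 100 × (1 − 0.49) = 51 (SD 7.141).
- Ratio to the change score: 51 / 60 = 0.85, which is (1 + ρ)/2. It is below 1 for any ρ below 1.

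**Step 3. Patient-level power at 105 completers per arm.** SE = √(2 × variance / 105); power = Φ(3/SE − 1.96).

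- Change score: SE 1.069, power 80.1%, difference detectable with 80% power 3.00.
- Adjusted for T1: SE 0.986, power 86.1%, detectable difference 2.76.

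Using the t distribution gives 79.8% and 85.8%.

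**Step 4. If the correlation is below 0.7.** At ρ = 0.5 the variances are 2 × 100 × 0.5 = 100 and 100 × 0.75 = 75, a ratio of 0.75. Power is 58.5% against 70.9% (58.1% against 70.5% with the t distribution).

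**Step 5. Sensitivity to clustering.** The documents give no intracluster correlation (ICC), so these values are assumed. With 210 completers in 12 units there are 17.5 per unit, and the design effect is 1 + 16.5 × ICC. Both variances are multiplied by it, which takes the unit-level T1–T2 correlation to be 0.7 as well. The reference distribution is t with 12 − 2 = 10 df.

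| Assumed ICC | Design effect | Power, change score | Power, T2 adjusted for T1 |
|---|---|---|---|
| 0.01 | 1.165 | 65% | 72% |
| 0.02 | 1.33 | 59% | 66% |
| 0.05 | 1.825 | 47% | 53% |

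**Step 6. If differences between units persist from T1 to T2.** Here the unit-level T1–T2 correlation is varied, with the overall correlation and the adjustment slope held at 0.7. Entries are the ratio of adjusted to change-score variance.

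| Assumed ICC | Unit-level correlation 0.5 | 0.7 | 0.9 | 1.0 |
|---|---|---|---|---|
| 0.01 | 0.84 | 0.85 | 0.87 | 0.88 |
| 0.05 | 0.82 | 0.85 | 0.92 | 0.97 |
| 0.10 | 0.81 | 0.85 | 0.96 | 1.10 |

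The advantage shrinks as unit differences become more stable. It reverses only in the most extreme cell examined.

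**The case against.** The strongest defence is that nothing here is stated wrongly. The hypotheses in section 3.2 speak of differences in mean score, section 3.6 is sized on the change score, and section 3.11 analyses it. The three agree. That stands: this is a point about efficiency, not an inconsistency.

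Second, a MANCOVA has covariates by definition, and an article may leave the list to a fuller document. If T1 is on that list, there is no loss: regressing T2 − T1 on group and T1 gives exactly the same group coefficient as regressing T2 on group and T1. This also stands as a possibility. But nothing in the text names T1 as a covariate, and the sample size does not use it. One sentence would settle the matter.

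Third, the change score already uses most of the correlation. Against T2 alone (variance 100), it removes 40 of the 49 units that adjustment would remove. A reader might infer that the correlation of 0.7 is wasted; it is not. What remains is the step from 60 to 51.

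A reader might also infer that change scores over-correct any T1 imbalance. That holds for chance imbalance. Here patients are recruited after their unit has been allocated, and T1 follows the first nurse meeting. An imbalance could therefore be stable or arise from selection, and a slope of 0.7 could then under-correct it.

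Finally, it is tempting to add that the QPC total, which includes a hospital-discharge dimension ("therapeutic relationship, patient participation, support received, environment, safety and hospital discharge"), cannot be rated properly at T1. The documents do not show the items or say that they cannot be answered early, so this is conjecture and forms no part of the point.

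**Conclusion.** The point holds as a recommended improvement. The planned analysis is valid, and the 131 per group is correct for it under individual-level assumptions. It is less efficient than adjusting for a score the trial already collects.

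Under section 3.6's own values the gain is 15% in variance, or about 6 percentage points of patient-level power (80% to 86%). It rises to about 12 points if the correlation is 0.5. This rests on equal SDs at T1 and T2, 105 completers per arm, and T1 not already being an unlisted covariate. The clustered figures rest in addition on assumed ICCs and on 10 df, which ignores the pairing of units. They show the direction and rough size of the effect and are not forecasts.

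Two further readings should be resisted. The lower requirement of 89 completers does not mean that the trial can recruit fewer patients, because clustering is not yet allowed for. Nor does this point require T1 to be moved. The timing of T1 is a separate data-collection question. Any early effect already present at T1 is subtracted in full by the change score and only to about 0.7 by adjustment, so the late T1 is no reason to prefer the change score.

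**What to change.** In section 3.11, for WAI-S and QPC, state that the T2 score is the dependent variable and the T1 score of the same scale is a covariate. Equivalently, keep the difference and add T1 as a covariate. Place this within whatever model accounts for unit. If T1 was always meant to be among the MANCOVA covariates, say so.

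In section 3.6, keep 131 per group. Note that it was derived from the change-score variance and that the adjusted analysis leaves a margin against clustering or a correlation below 0.7.

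State separately how CES will be analysed. It has no T1 score, so neither a pretest-posttest difference nor this adjustment is available for it.

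For WAI-S and QPC the cost is a change of analysis wording, with no new data, visits or patients.

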### Ethical considerations

3.12

This project has received approval by the bioethics committee of the ‘REDACTED’ and by each of the reference ethics committees for each of the other participating institutions. The consequent authorization will be requested from all participants for the public result that will be given to the data, preserving anonymity and strict confidentiality at all times, and therefore the name of the participants will be coded and numbered. The data obtained will be incorporated into an electronic database and the information provided will be treated as completely confidential. Any data or name that might reveal the identity of the informants will be eliminated. The persons who participate will do so voluntarily, signing the corresponding consent of acceptance of the study conditions, with the right to withdraw from the study at all times.

### Validity and reliability/rigour

3.13

#### Study protocol

3.13.1

The methodology for conducting this protocol follows the guidelines set out in the 2013 SPIRIT Statement (Chan et al., 2013). This study has been registered in www.clinicaltrials.gov under the code NCT05220566. Funding was granted in 2021 by the Instituto de Salud Carlos III (PI21/00605)), and by the College of Nurses of Barcelona (PR‐487/2021), after a peer‐reviewed funding process. This project is also co‐funded by the European Regional Development Fund (ERDF).

